
| Project implementation |
| --- |

| **METHODOLOGY**  **General aspects**  This will be an open, prospective, randomised controlled trial with three parallel arms.  The study will concern all GPs in the Loire-Atlantique *département*, France applying the inclusion and non-inclusion criteria, and their female patients aged from 40 to 65 years who are eligible for cervical cancer screening.  The randomisation unit will be the medical practice, identified by its address. Randomisation will thus be performed on the place of practice rather than the practitioner to avoid confusion bias between arms. Thus several practitioners practising in a given place of practice will be assigned to the same arm, either "List to GP + letter to patients", "letter to patients alone", or "screening on individual initiative ".  The statistical unit will be the patient.  The analysis will be intention-to-treat. The study will be conducted in "real life" conditions taking account (and reporting on) of the fact that a given intervention has variable impact depending on the practitioners targeted by the intervention.  **Study population**  Inclusion criteria  The GPs eligible for this study will be individuals who do not have *Mode d'Exercice Particulier* status (complementary and alternative medicine), practising in Loire Atlantique. The list of the GPs in this territory will be derived from CRCDC Pays de Loire (cancer screening coordination centre). The population of eligible GPs is estimated to amount to 1500.  Eligible patients will have the following characteristics:  - Age 40 to 65  - Affiliated to a health insurance system  - Present on the list of a participating GP  - Residing in Loire Atlantique.  In practice, the list of patients will be derived from CRCDC Pays de Loire; their database collects information from the different health insurance bodies (*Régime Général, Mutualité Sociale Agricole*, other).  In Loire Atlantique the target population was estimated in 2019 to amount to 233 500 women (French public health data).  Non-inclusion and exclusion criteria  The GPs will receive information on the implementation of the survey 3 months before it starts, and will be able to contact the CRCDC data protection delegate if they wish to refuse to participate. The GPs who refuse to participate will not be included and thus will not be assigned to any arm in the process of randomisation (see also section on ethics and non-opposition).  Patients with a history of total hysterectomy and those with a pathological smear result will not be eligible for screening and excluded.  Women who have not named an attendant GP (*médecin traitant*) will not be included. In Loire-Atlantique the percentage of insured individuals who have not named their attendant GP has been estimated to be between 7 and 15% on the basis of health insurance data, the figure being variable from one territory to another. The percentage specifically aggregating the population of women aged 40 to 65 years is not available).  **Randomisation, intervention arms and control arm**  Randomisation will concern medical practices, so that practitioners will be distributed across the three arms.  On the basis of the list of practitioners assigned to the different arms, the CRCDC will draw up a list of names of women eligible for cervical screening aged 40 to 65 for each GP, excluding patients meeting non-inclusion criteria.  Thus when randomisation is complete, participating GPs and their patients will be randomly assigned to one of the three following arms:  "optimised cancer screening" group  • The GPs will receive a list of their patients aged 40 to 65 who have not undergone cervical cancer screening in the last three years, with specific attention to factors of non-participation.  • The patients will receive a letter: 1) inviting them to obtain an appointment with a health professional (GP, midwife, gynaecologist) to undergo a screening test, and 2) specifying that the screening procedure cost will be covered 100%.  "standard cancer screening" group  • The GPs in this arm will not receive the list of their patients aged 40-65 who have not undergone cervical cancer screening in the last three years.  • The patients will receive a letter: 1) inviting them to obtain an appointment with a health professional (GP, midwife, gynaecologist) to undergo a screening test, and 2) specifying that the screening procedure cost will be covered 100%.  "usual care" group  • The GPs in this arm will not receive the list of their patients aged 40-65 who have not undergone cervical cancer screening in the last three years.  • The patients will not receive a letter from CRCDC. The consultation and the test will be reimbursed as normal by the health insurance system and the complementary insurance.  **NB** The patients aged 40-65 who have not undergone cervical cancer screening in the last three years will be identified by way of the absence of health insurance reimbursement for the intervention.  In practice, the list of patients will be derived from the Pays de Loire CRCDC database, which draws its information from the health insurance bodies (*Régime Général, Mutualité Sociale Agricole*, other).  For Loire-Atlantique, the number of patients aged 40 to 65 who have not undergone a cervical smear test in the last three years was estimated in 2019 to be 130 300 (public health data).  **Main and secondary judgement criteria**  A. **The primary endpoint** is the proportion of women aged 40 to 65 who are up-to-date with their screening (having performed a screening test in the last 3 years) 6 months after the intervention. The 6-month duration takes into account the capacities of professionals to respond to a consultation request for this type of medical procedure.  **B. Secondary judgement criterion**  - the proportion of cytology examinations carried out among all tests performed, the proportion of HPV tests carried out among all tests performed, and the proportion of tests yielding abnormal results (cytology, HPV) among all tests performed.  - the percentage of “reflex tests” conducted among abnormal tests at 6 months.  - the percentage of biopsies and conizations carried out among the abnormal screening tests in the 12 months following the intervention.  - the percentage of high-grade lesions detected (second, a third-grade cervical intraepithelial neoplasia, including in situ carcinomas and cancers) among the abnormal screening tests in the 12 months following the intervention.  - the rate of treatments carried out (conization, laser, hysterectomy) among the abnormal screening tests in the 12 months following the intervention.  - Participation rate according to age (over 50), income (women with low incomes qualifying for basic health coverage) and comorbidities.  - the proportion of women having consulted a GP, a midwife or a gynaecologist for a screening test.  - the time period between posting the letter and the date of the screening test.  **Data collection**  The data will be collected or extracted via complementary, coordinated means:  **• Some of the data will be collected from CRCDC** via routine methods:  - Identification of patients eligible for organised screening who have named an attending GP meeting the inclusion criteria for GPs  - Patients having undergone screening or an HPV test (date of the examination in this case) in the 12 months following inclusion.  - Patient's address and IRIS code so as to attribute a European Deprivation Index score.  The study will process data transferred between the health insurance body and CRCDC as defined in the national references: "Types and contents of files required for the creation of databases for cervical cancer screening" (INCa September 2018).  Administrative and socio-demographic data enabling the characterisation of the women:  • Family name • Given name(s) • Date of birth (DD/MM/YYYY) • Address • Post code, town • Health insurance body • Email • Named attending GP • Identification number of the named practitioner • Universal health cover status (CMU) (yes/no).  Variables enabling identification, for each woman, of the medical acts performed in the setting of cervical cancer screening:  • Date of the act • Code of the act • Identification number of the practitioner performing the act • Identification number of the prescribing practitioner   - Data specifically collected from the health insurance system:   . Characteristics of the GPs: age, gender, classification of the practice locality, activity in numbers of acts per year, convention sector (1,2), practising alone or in a group  . Patient characteristics: CMU status, long-term illness (ALD) and CS status (assistance in contracting a complementary health insurance) (with a view to adjusting analyses of these variables).  . Number of consultations with a GP/ gynaecologist a) in the 24 months before the dispatch of the invitation letter and b) in the 12 months following the dispatch of the letter.  **Statistical analysis**  **1. Description of the statistical methods planned**  All the data will be described globally and per randomisation arm. The statistical unit will be the woman eligible for screening. The significance threshold will be set at 5%.  The analyses will be performed using R 3.6.0. software (R Foundation for Statistical Computing, Vienna, Austria. URL <https://www.R-project.org/>.)  **Main criterion**  The percentage of women up-to-date with their screening 6 months after the intervention will be compared across arms using a generalised mixed linear model to adjust the analysis on the random effect of the GP.  A hierarchical procedure will be used to successively test the comparisons of the three arms, controlling for type I error.  The first hypothesis tested will be the difference between the intervention arms (“optimised organised cancer screening” and “standard organised cancer screening”) and the "usual care" arm. If the result is significant, a second test will be conducted, comparing the "optimised screening" arm with the "standard screening" arm.  **Exploratory secondary analyses**  The types of tests conducted and the types of professional consulted will be described and compared between arms using the same models as for the main criterion. The time-lapse to screening uptake will be described and compared using a mixed Cox model adjusted for the type of professional chosen, the randomisation arm and the GP as a random effect. The percentages of cytology tests and HPV tests conducted in the following 6 months and the percentage of abnormal tests among all the screening tests will be calculated and compared between the different arms using a generalised mixed linear model adjusted on the GP. The same will apply to the percentage of "reflex tests" conducted among the abnormal tests at 6 months, to the percentages of biopsies and conizations carried out among the abnormal tests in the ensuing 12 months, to the percentage of high-grade lesions detected (second- and third-grade cervical intraepithelial neoplasia, including in situ carcinomas and cancers) among the abnormal screening tests in the ensuing 12 months and to the percentages of women resorting to each type of professional.  A generalised mixed linear model will be used to assess factors associated with screening uptake among the following: age of the woman; low economic status; long-term illness status; the French DEPrivation index of the place of residence; and the number of visits to GPs, midwives or gynaecologists during the follow-up period.  **2. Statistical justification of the sample size**  Over the 2017-2019 period, the screening participation rate in Loire-Atlantique was 61.3% and concerned approximately 154 000 women (internal source: regional organisation in charge of cancer screening). On the basis of data from the literature, the research team estimates that the proportion of women who will undergo a screening test while not having had a smear test for over 3 years could reach 25%, thanks to the letter sent to their GP that includes the list of his or her non–up-to-date patients ("optimised" arm), whereas the increase in participation should be more limited in the "standard screening" arm (15%) and nil in the "usual care" arm. After the intervention, participation rates should therefore be 71% in the "optimised screening" arm, 67.1% in the "standard screening" arm and 61.3% in the "usual care" arm.  In September 2020, there were 1 395 GPs in the Loire-Atlantique, with an average of 2.15 GPs per medical practice. The multiplication factor derived from the cluster randomisation is defined at 12.8 (intra-class correlation coefficient: 0.05). Inclusion should reach a minimum of 37 776 patients per arm to demonstrate a difference between the "optimised" arm and the "standard" arm. As a total of 154 000 eligible women will be included in the study, we will be able to demonstrate this difference with 51 300 women per arm.  **3. Randomisation**  The practices of the GPs will be randomised in the three parallel arms (cluster randomisation) with a 1:1:1 ratio. Each GP will be linked to the randomisation arm and his or her place of practice, and each patient to the randomisation arm of her attending GP.  **Piloting of the project and the roles of the different players**  **Steering Committee**  The project will be coordinated by [name].  [name] [name] is the project deputy coordinator.  The collective expertise is ensured by the Steering Committee which will gather all the partners  This Committee will define the general organisation and deployment of the project, will coordinate information and will decide on how to proceed in case of unexpected events.   - [name], project coordinator for Nantes University - [name], deputy project director, for CRCDC Pays de la Loire - [name], in charge of statistical studies, for the health insurance body   **Roles of the different people involved**  Department of general medicine  Throughout the study, the coordination will be ensured by [name] (Nantes University, INSERM U 1232, team 2). He will be in charge of the design and drafting of the final protocol for the randomised trial, the drafting of intermediate reports and the final scientific report, and of the scientific valorisation of the trial.  CRCDC  CRCDC represented by [name] will ensure the study coordination.  It will take part in all stages in the research, from the design of the protocol for the randomised trial to its final scientific valorisation. It will be in charge of collecting information from the different sources, and of dispatch of the letters to the eligible women and the GPs. It will have the task of updating the status of each patient with respect to organised cervical cancer screening. The CRCDC will be in charge of the database. It will be in charge of the transfer of data to the research teams.  The Nantes CHU (university hospital) clinical research directorate (DRC)  The Nantes CHU DRC methodologist and biostatistician will ensure that the methodology of the statistical analyses is complied with. She will be in charge of drawing up the randomisation list, of the analysis of all the data from the randomised trial using the anonymised data transferred by CRCDC.  The DRC teams will be in charge of legal procedures and requirements.  Health Insurance bodies  As in the IDLN study ([15,29] a partnership will be established with the health insurance bodies.  They will provide the CRCDC with the data that is routinely transferred, and will also include certain data specifically collected in the setting of the present study (see Data Collection section)  The health insurance bodies will provide their expertise in the identification of medical acts and the tracing of healthcare trajectories using information in their databases.  **Legal requirements, ethics committee and non-opposition by participants**  The Jardé legislation does not apply to this study. The research does not involve human beings directly, since it aims to evaluate modes of practice among health professionals.  1. Computerised data and CNIL approval  The data processing will be registered in the Nantes CHU data protection body (RGPD).  The data collected in the course of the study will be stored in a computerised file in compliance with the "informatique et libertés" legislation of January 6th 1978, modified by legislation n° 201#8-493 dated 20th June 2018 relating o the protection of personal data, and with the European parliament legislation 2016/679 and that of the European Council dated 27th April 2016 relating to the protection of individuals with respect to the processing of personal data and the free circulation of that data.  The protocol belongs to the field of methodology (reference MROO4 with which Nantes CHU complies.)  2. Ethics approval  The experimental protocol will be evaluated in view of the ethical requirements. The study does not come under Jardé[[1]](#footnote-2) requirements. The project will be submitted to prior approval by the Ethics Committee assessing non-RIPH projects like that of the Collège National des Généralistes Enseignants (CNGE).  3. The principle of non-opposition in the setting of a study aiming top assess new procedures in public health.[[2]](#footnote-3)  At least 3 months before the first inclusion, the GPs will be informed by letter about this pilot study on cervical cancer screening. They will be invited to signal their refusal if they do not wish to participate. In the absence of explicit refusal by a GP, he or she will be included in the study.  This mode of collection of non-opposition will be conducted in compliance with international ethical requirements for studies aiming to assess new procedures in the area of public health. International recommendations stipulate that explicit consent can be waived when the study concerned meets the following: 1) The research is designed to evaluate possible changes in public health programmes, and 2) The research cannot practicably be carried out without the waiver.  The mode of implementation will follow that agreed by CNIL, CPP and various international players (clinicaltrials.gov, JAMA) for the IDLN study previously funded by the National Cancer Institute (France)  **Data collection and anonymity**  CRCDC- Pays de la Loire will collect the study data.  Initially, the CRCDC Pays de Loire computing department (ZEUS database) will be in charge of the request to form the populations for the three arms.  The data will be centralised by CRDCDC.  The methods of transfer of data between the health insurance and the regional cancer screening coordination centre will be those in routine use.  CRCDC will transfer an anomymised database comprising a patient identifier code, but no data identifying the person, to the person in charge of the analysis (dates replaced by periods)  **Data collection - quality control**  CRCDC will collect data over the 12 months following the intervention.  CRCDC- Pays de la Loire will produce the data described above, drawing on the data transferred by the health insurance.  **Management and analysis of the data and valorisation**  The data analysis will be conducted under the responsibility of the study methodologist and biostatistician, on a database transferred by CRCDC. The valorisation of the results will be conducted via collaboration among the individuals involved in the study, commensurately with their implication and responsibilities at the different stages.  **Project implementation calendar**  **Provisional calendar**  The project is planned to run over 36 months.  **M-4** **to M-2:**  - Legal procedures, registration of the study in Nantes CHU RGPD register, submission of the project to the ethics committee, registration of the trial on clinicaltrials.gov.  - The health insurance body transfers to CRCDC the list of non-MEP GPs practising in Loire Atlantique (this information circuit is already established between the health insurance bodies and CRCDC).  - Transfer to CRCDC by the different health insurance bodies of information relating to women aged 40 to 65 residing in Loire Atlantique (this information circuit is already established between the health insurance bodies and CRCDC):  . Name, first name, date of birth, Social Security number, address of place of residence (data that is routinely transferred), name of GP  . Presence of a medical act enabling identification of a cervical cancer screening test (according to standard codes) in the course f the last 3 years  . ALD (long illness), CMU (universal health cover) and ACS (complementary health cover allowance) status.  **M-2 à M-0**:  - CRCDC generates an inclusion code per medical practice and transfers the coded list to the methodologist and statistician.  -The methodologist statistician carries out the centralised randomisation of the addresses of places of practice of GPs to 3 parallel arms, and transfers the result of the randomisation to CRCDC. This procedure avoids the transfer of names attached to data to the coordinator's team. The name-linked data remains with CRCDC, as is usual with respect to CNIL requirements.  **M0-M2**: Intervention in arms 1 and 2:  In the arm "lists to GPs AND letter to patients"  . For patients not having undergone cervical smear in the last 3 years dispatch of the letter inviting them to undergo a screening test covered 100% by the health insurance  AND  . Parallel dispatch to each GP of a list of the names of their patients who have not undergone a smear test in the last 3 years  In the arm "Letter to patients":  . For patients not having undergone cervical smear in the last 3 years dispatch of the letter inviting them to undergo a screening test covered 100% by the health insurance  No list of patients is however sent to the GPs.  In the arm "Individual screening initiative ":  . No letter is sent to women who have not undergone a screening test in the last 3 years  . No patient lists are sent to the GPs.  **M10**: Closure of the database relating to follow-up data for the main criterion (occurrence of a screening test)  **M10 to M12: Analysis of the main judgement criterion – intermediate report on participation**  **M20**: Closure of the database relating to anatomo-pathological data and other secondary criteria. Transfer by CRCDC to the coordinator of a file with anonymous individual data relating to participating patients.  **M20 to M26**: **Analysis of the secondary criteria** concerning anatomo-pathological data, the care trajectory, and factors associated with lesser participation.  **M26 to M29:** Drafting of the final report  **M29 to M32:** Drafting of scientific articles and follow-up to publication   | **Actions** | **M-4 to M-2** | **M-2 to M-0** | **M0 to M2** | **M10** | **M10 to M12** | **M20** | **M20 to M26** | **M26 to M29** | **M29 to M32** | | --- | --- | --- | --- | --- | --- | --- | --- | --- | --- | | Legal procedures | X |  |  |  |  |  |  |  |  | | Identification of eligible women by CRCDC | X |  |  |  |  |  |  |  |  | | **Randomisation** of GPs to 3 parallel arms |  | X |  |  |  |  |  |  |  | | **Intervention**: dispatch of letters in arms 1 and 2 |  |  | X |  |  |  |  |  |  | | Closure of database for main criterion |  |  |  | X |  |  |  |  |  | | **Analysis of main criterion** |  |  |  |  | X |  |  |  |  | | Closure of database for secondary criteria |  |  |  |  |  | X |  |  |  | | **Analysis of secondary criteria** |  |  |  |  |  |  | X |  |  | | Drafting final report |  |  |  |  |  |  |  | X |  | | Scientific valorisation |  |  |  |  |  |  |  |  | X | |

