| **1/ Expected results**  Our study should lead to an increase in uptake of organised cervical cancer screening as a result of sending GPs a list of their patients aged 40 to 65 who have not undergone a test in the last 3 years in comparison to 1) only sending a letter to women who are not up to date (routine in organised screening) or 2) no letter sent to GPs or their patients.  In view of the previous literature (13,14,15,16), the increase in screening uptake could reach respectively 25% and 15% in the optimised and standard organised cancer screening groups. The number of eligible patients identified (n= 94 393; 2020) should be sufficient to show a difference between the “optimised screening” and the “standard screening” arms. On the basis of an initial screening uptake of 61.3% in the general population in the third arm ("usual care"), increased participation could thus reach an absolute value of (1–0.61) × 25% in arm 1 and (1–0.61) × 15% in arm 2, corresponding to 9.7% and 5.8%, respectively. The calculation of the NNT (number needed to treat) we propose to use is set out in the section Statistics – justification of the numbers to include.  At a time when organised screening is being set up on a national scale:   - This project will provide a tool to back up practice among GPs, in the context of the decision in the national Cancer Plan to make GPs the coordinators of screening. - The project adds to the various modes of intervention available to decision-makers to increase uptake of cervical cancer screening. - This project enables the evaluation of the trajectories of women who undergo a test after receiving the letter while they have not undergone one for the last 3 years. It will enable a description of resort to care in terms of the professionals consulted and the time-lapse to access to care. - This project finds its place in the dynamic of organised screening on the scale of a regional territory (Loire Atlantique), where the participation rate is already higher than the national rate. - This project affords a unique opportunity to analyse the effects of the implementation of organised screening using a scientific method - A robust design, based on a randomised trial, unprecedented in the area of cervical cancer screening. - A study with considerable power, since the analysis concerns the whole population of a whole *département*. We found no other study on this scale in the literature. - Our project will produce results that will be reproducible, since the design is in intention to screen, and the intervention tested is straightforward and inexpensive - With respect to the research dynamic, this project will back up the dynamics of collaborative work among the main players in care strategies and screening in primary care: GPs, CRCDC, the health insurance bodies, the CHU   **2/ Method of evaluation**  The method of evaluation used will be a reference scientific method deploying a large-scale randomised trial for the main criterion. The other evaluation criteria (secondary) will be the subject of scientific analyses according to reference methods (see also the section Statistic).    The participation rate will be compared across arms using generalised linear models to take account of the cluster randomisation.  The proportion of abnormal smear results and positive HPV tests, and the time to consultation according to the professional chosen, will be described and compared across the three arms.  Factors associated with non-participation will be analysed using multivariate linear regression.   - Evaluation of the participation rates at 6 months:   Participation rate = number of screening tests (cervical smear or HPV test) / Number of patients targeted by organised screening   - Results of screening tests - Total number of cervical smears or HPV tests with results - % of unsatisfactory cervical smear tests /HPV tests - % of positive cervical smear tests /HPV tests - The screening activity per speciality will be described, reporting the number of cervical smears performed and the number of HPV tests per practitioner speciality: GP, gynaecologist, midwife, other (laboratory)     **3/ Indicators for project follow-up and for results, mode of evaluation of the quality of the action undertaken, etc**  Project follow-up indictors:  Compliance with the different stages in implementation as described in the project calendar  Results indicators:  Number of women eligible for screening  Number of letters sent to arms 1 and 2  Number of screening tests performed at 6 months  Number of abnormal test results in the 3 arms.  Evaluation of the quality of the actions undertaken  The study we propose is a large-scale randomised trial in the general population, with a robust design and very good reproducibility*.* |

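### Practices are randomised, but the primary model has a random effect for the GP only, so correlation shared within a practice is missing from the standard errors

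*Protocol*

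**What the plan says.** In the Protocol's Methodology, General aspects, the unit of allocation is explicit: "The randomisation unit will be the medical practice, identified by its address". The same paragraph adds that "several practitioners practising in a given place of practice will be assigned to the same arm".

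Under Statistical analysis, 1, Main criterion, the percentage of women up to date at 6 months is to be "compared across arms using a generalised mixed linear model to adjust the analysis on the random effect of the GP". The exploratory analyses that follow either refer back to this model or name the GP again, and the Cox model for time to screening also has the GP as its random effect. No practice term and no practice-level robust variance appears anywhere.

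Under Statistical analysis, 2, the sample size section states: "The multiplication factor derived from the cluster randomisation is defined at 12.8 (intra-class correlation coefficient: 0.05". It gives 1,395 GPs, 2.15 GPs per practice and 154,000 women.

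Under Evaluation of results, 2/ Method of evaluation, the wording is more general: "The participation rate will be compared across arms using generalised linear models to take account of the cluster randomisation". No cluster level is named there.

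**The concern.** In a cluster-randomised trial the arm comparison varies with the unit that was allocated. If women registered with different GPs at the same address have correlated screening behaviour, a model with a GP effect only treats about 1,395 GPs as independently allocated, when about 649 practices were. The practice-level part of the variance is then counted as if it averaged out over twice as many units. Standard errors come out too small, confidence intervals too narrow, and a null effect is declared significant more often than planned.

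This concerns the primary test. The hierarchical sequence (intervention arms against usual care, then optimised against standard) is presented as controlling type I error, but it can do so only if each test in it holds its own level. The second step is the trial's main novelty, the list sent to GPs.

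**Working it through.** **Inputs from the Protocol, sample size section:** 1,395 GPs; 2.15 GPs per practice; 154,000 women; ICC 0.05; design effect 12.8; 71% against 67.1% for optimised against standard; minimum 37,776 per arm; 51,300 per arm planned.

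**1. Which level does the design effect use?**
- Practices: 1,395 / 2.15 = 649. Women per practice: 154,000 / 649 = 237.3. Design effect: 1 + 236.3 × 0.05 = 12.82, which matches the stated 12.8.
- Women per GP: 154,000 / 1,395 = 110.4. Design effect: 1 + 109.4 × 0.05 = 6.47, which does not match.

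The stated number per arm follows from the practice-level factor. Power and sidedness are not stated. Assuming 90% power and two-sided 5%, the usual two-proportion formula for 71% against 67.1% gives 2,951 per arm, and 2,951 × 12.8 = 37,773 against 37,776 stated.

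**2. What does a GP-only model leave out?** Let ρ = 0.05 be the correlation between women of the same GP, f the share of it that also holds between women of different GPs in one practice, m = 110.4 and k = 2.15. With equal sizes, the true variance of an arm comparison relative to the one the GP-only model reports is

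1 + (k − 1) × fρ / [ρ + (1 − ρ)/m], where ρ + (1 − ρ)/m = 0.05 + 0.95/110.4 = 0.0586.

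The type I error is 2 × [1 − Φ(1.96 / √ratio)].

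| Share f of the correlation common to the practice | Variance ratio | Reported SE / true SE | Two-sided type I error |
|---|---|---|---|
| 0% | 1.00 | 1.00 | 5.0% |
| 10% | 1.10 | 0.95 | 6.1% |
| 20% | 1.20 | 0.91 | 7.3% |
| 25% | 1.25 | 0.90 | 7.9% |
| 50% | 1.49 | 0.82 | 10.8% |
| 75% | 1.74 | 0.76 | 13.7% |
| 100% | 1.98 | 0.71 | 16.4% |

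**3. Unequal practice sizes.** The Protocol gives only the mean of 2.15. Assuming a coefficient of variation of 0.5 in GPs per practice, k is replaced by 2.15 × (1 + 0.5²) = 2.69. The error becomes 6.7%, 8.4%, 9.3%, 13.5%, 17.4% and 20.9% for f from 10% to 100%.

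A simulation under a null effect used 649 practices, 1 + Poisson(1.15) GPs each, 110 women per GP and 2,000 runs. It compared GP means rather than fitting the mixed model. Treating GPs as independent, it rejected in 9.7%, 13.8%, 17.2% and 19.1% of runs for f = 25%, 50%, 75% and 100%. With practice-clustered standard errors it rejected in 4.5% to 5.9%.

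**4. Sensitivity to the number of women.** The Protocol's objectives give 94,393 eligible women instead of 154,000. Then m = 94,393 / 1,395 = 67.7, and the equal-size error at f = 100% is 15.5% instead of 16.4%. The point does not depend on which figure is used.

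**5. Interval width for optimised against standard, 51,300 per arm.** The binomial variance term is 0.71 × 0.29 + 0.671 × 0.329 = 0.4267.
- Design effect 12.8: SE = √(0.4267 × 12.8 / 51,300) = 1.03 points; 95% half-width 2.0 points.
- Design effect 6.47: SE = 0.73 points; half-width 1.4 points.

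If the correlation is practice-wide, an observed difference between about 1.4 and 2.0 points would be called significant when it should not be.

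**The case against.** **The inflation is conditional.** It needs positive correlation between women of different GPs at one address, and the Protocol never states that quantity. Applying one ICC to a whole practice is a common planning simplification and does not show where the variance lies. The Protocol also expects the intervention's impact to vary with the practitioner, which points to some GP-level variance. A reader might infer that the 5% level is certainly lost, or that 16% is the expected error. The documents support neither: 16% is what the sample size assumption implies, and smaller values follow from partial sharing. This stands, and it is why the result is given as a range.

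**The planned effects are large.** With the practice-level factor, 71% against 67.1% gives z = 3.9/1.03 = 3.8, and 67.1% against 61.3% gives z = 5.8/1.07 = 5.4. If the effects are as planned, the conclusions would probably not change. The risk lies with null or small effects and with interval width.

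**Not every secondary comparison is equally affected.** Those analyses are labelled exploratory, and type I control is claimed for the main criterion only. Several have abnormal tests as their denominator, so there are few women per GP. Even at f = 100% with equal sizes, the same formula gives 7.8% with 5 women per GP, 6.3% with 2 and 5.7% with 1 (assumed denominators). The model for factors associated with uptake names no random effect, so a GP-only effect cannot be attributed to it.

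**The evaluation section states the right purpose.** It would be wrong to read it as dropping the clustering, since it says the models are to account for the cluster randomisation. But it names no level, so it does not override the specific statement under Main criterion.

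**GP may be shorthand for the randomised unit.** The calendar does speak of randomising GPs. Elsewhere, however, the Protocol separates GP from practice, and the model sentence names the GP. An analysis plan with a practice effect would have to depart from that sentence.

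**Conclusion.** The mismatch holds on the Protocol's own text: practices are allocated and the sample size is inflated at practice level, but the primary model accounts for clustering by GP only. Correlation shared between GPs of one practice is left out of the standard errors.

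Given a total ICC of 0.05 and the Protocol's cluster numbers, the plausible type I error of each primary comparison runs from just above 5% to about 16% with equal practice sizes, and to about 21% with the assumed variation in size. The split of the ICC and the spread of practice sizes are assumptions. The direction is not in doubt for any positive practice-level correlation, and the planning assumption itself implies such correlation. Secondary models that name the GP share the flaw, to a lesser degree where denominators are small.

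This should be corrected before analysis, because it affects the validity of the primary test and the remedy is simple.

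**What to change.** - **Primary model (Main criterion):** replace the GP random effect by a random effect for the medical practice as the randomisation unit, with GP nested within practice. A practice-clustered robust variance would also serve.
- **Secondary analyses:** make the same change in the generalised mixed models and the Cox model that name the GP.
- **Evaluation of results, 2/ Method of evaluation:** state that the cluster is the medical practice.
- **Data transfer:** state that the anonymised analysis file carries the practice code. The calendar shows that the screening coordination centre already creates one code per practice for the randomisation.

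The cost is a sentence in each place and somewhat wider confidence intervals. The sample size need not change, because it is already based on practices: at 51,300 per arm with the 12.8 factor, power for 71% against 67.1% is about 96.5%.
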